## Materials and methods

### Participants

This pilot study will be conducted with children and adolescents of any gender and psychiatric diagnoses who currently are inpatients in Austrian child and adolescent psychiatric institutions cooperating with RED NOSES Clowndoctors Austria. Specific inclusion criteria are (1) being aged between 7 and 18 years and (2) regular participation in clown visits at the relevant health care facility on a weekly basis. Exclusion criteria are (1) potential negative impacts of clown visits or study participation on participants’ mood or well-being according to medical or paramedical care staff of the relevant health care facility and (2) insufficient command of German (for self-administered questionnaires only).

Participants will be recruited from two cooperating psychiatric healthcare facilities in Austria. The visits will take place in at least two different wards of each participating psychiatric care facility. In each ward, a maximum of 10 participants will be targeted. The four-week intervention assessments will take place twice in both clinics with different patients (time interval of approximately four to seven weeks between the two assessment phases). The first recruitment phase is initiated by a staff member of RED NOSES Clowndoctors, who regularly visits those clinics. Within the clinics, the recruitment process will be assisted by the care staff of the relevant wards. After being informed about the study goals and data collection process, care staff will evaluate the eligibility of specific patients regarding potential negative impacts of clown visits or study participation. If there are no anticipated negative consequences on participants’ health or well-being, informed consent will be obtained from participants and, in case of underage participants, their parents or legal guardians prior to the start of data collection.

Based on effect sizes reported in reference studies [18, 33–39] we computed the minimum sample size needed for identifying the expected effects assuming rudimentary paired one-tailed t-tests using G*Power [40]. Calculating with β = .20, α = .05, and expected effect sizes for cortisol levels (*f* = .25), self-administered measures of stress (*f* = .44), anxiety (*f* = .47), and emotional state (*f* = .23), a minimum sample size of about 30 participants in total (children and adolescents together) is needed. It is of note that the effect sizes for emotional state were derived from adult samples due to a lack of child and adolescent data. All other estimates were based on child samples. Accounting for dropout and random variation, a sample size of at least 50 children and adolescents will be targeted.

### Trial design

This pilot study uses a non-controlled pre-/post-test design. There is no control group and no variation in intervention to be evaluated; thus, the study contains only one arm. See Fig 1 for an overview of the study schedule according to the SPIRIT 2013 Statement [41].

**Fig 1 pone.0264012.g001:**
[figure not shown]
SPIRIT schedule.

### Procedure

At baseline, standardized questionnaires will be used to assess participants’ sociodemographic data, general mental and physical health status, emotional and conduct problems, perceived stress, and coping mechanisms. Participants will be administered paper-pencil versions of the undermentioned measures and will be asked to fill them out by themselves under supervision of the examiners. Additionally, the assigned care staff will provide basic clinical information for each participant in form of a self-administered questionnaire. In this session, participants will be assigned a pseudonymized code. Following baseline assessment, salivary cortisol as well as self-administered questionnaires on stress and mood states of participants will be collected before and after each clown visit on a weekly basis over four consecutive weeks. Immediately after the fourth clown visit, the self-administered questionnaires from the baseline assessing secondary outcome measures will be presented a second time. Effects on care staff at the health care facilities will be assessed within the same time period of four consecutive weeks based on a self-administered questionnaire completed after each clown visit. Fig 2 outlines the study procedure and assessments per time point.

**Fig 2 pone.0264012.g002:**
[figure not shown]
Study procedure.

### Intervention

Clown visits will be carried out routinely by two professional clown artists from RED NOSES Clowndoctors Austria once a week for four consecutive weeks either in a group setting or an individual setting. The selection of artists, type of setting (group or individual), duration of clown visits, and specific artistic sequences will correspond to usual clown visits in those institutions, following internally organized routines instead of being standardized. The essence of the clown visit is to catch the patient’s attention proactively and reach the highest possible level of engagement. The specific artistic sequences and type of setting are implemented spontaneously according to the situational atmosphere and current condition of participants. One clown visit in the group setting will last between 1 and 2 hours including individual as well as collective attention depending on age, number of participants, and situational atmosphere. In the individual setting, each participant will be engaged individually between 5 and 20 minutes by the clown, depending on the situational mood and condition of the patients. The clown artists are not involved in any study-related research activities.

### Primary outcome measures

#### Perceived stress

Subjective stress levels of children and adolescents will be assessed in a self-administered manner with one item (“Right now I am feeling stressed.”) using a 100-mm visual analogue scale (VAS) before as well as immediately after each of the four clown visits. The item asks participating children and adolescents to draw a line where they would currently place themselves on the VAS ranging from 0 (not at all stressed) to 100 (very much stressed). Age-appropriate anchor graphics are placed at both extremes to support comprehension. The VAS approach has been used and validated in a number of previous studies in stress research [42, 43].

#### Perceived mood

The original German short version of the self-administered Multidimensional Mood Questionnaire (MDMQ) [44] will be used to measure adolescents’ different dimensions of current mood states (pleasant–unpleasant; awake–sleepy; calm–restless) before as well as immediately after each of the four clown visits. The MDMQ provides four-item scales to measure each dimension. Participants respond to the statement “At this moment I feel…” by means of adjectives (e.g., “content”; “tired”; “agitated”; “well”) on a 5-point Likert scale from 1 (not at all) to 5 (very much). The validity and reliability of the measure have been shown [45]. For children aged between 7 and 11 years, we adapted the scale to an age-appropriate picture-based version with two items per dimension rated on a similar 5-point Likert scale from 1 (not at all) to 5 (very much).

#### Salivary cortisol

Saliva samples of cortisol are collected as a marker for the physiological stress response of children and adolescents. Salivary cortisol reflects the activity of the HPA axis. We will use Salicaps collection devices consisting of collection tubes and straws. Samples will be collected immediately before as well as immediately after each of the four clown visits in a self-administered way, but under the supervision of the examiners. Participants will be thoroughly instructed to collect accumulated saliva for two minutes without swallowing. After the two minutes, participants will transfer the accumulated saliva into the Salicap tube via the straw. Tubes are then stored locally at the health care facility at -20°C prior to transport to and analysis in the biochemical laboratory.

### Secondary outcome measures

#### Health-related quality of life

Children’s and adolescents’ health-related quality of life will be assessed at baseline and at close-out assessment immediately after the fourth clown visit by the self-administered German revised questionnaire Health-Related Quality of Life (KINDL-R) [46, 47]. We will use the three subscales *physical health* (sample items: “During the past week I felt ill” or “… I had a headache or tummy-ache”), *mental health* (sample items: “… I had fun and laughed a lot” or “… I was bored”), and *self-esteem* (sample items: “… I was proud of myself” or “… I felt pleased with myself”). Each subscale consists of four items rated on a 5-point Likert scale from 1 (never) to 5 (always). Age-appropriate versions of the questionnaire are used for children and adolescents. The validity and reliability of the German self-administered version have been demonstrated [48].

#### Emotional and conduct problems

Children and adolescents will complete the five-item emotional problems and conduct problems subscales of the self-administered Strengths and Difficulties Questionnaire (SDQ) [49] adapted for use in German [50] at baseline and at close-out assessment immediately after the fourth clown visit. Sample items assessing *emotional problems* are: “I am often unhappy, depressed, or tearful” or “I have many fears; I am easily scared”. Sample items measuring *conduct problems* are: “I take things that are not mine (from home, school, or elsewhere)” or “I get very angry and often lose my temper.” Responses are 0 = not true, 1 = somewhat true, and 2 = certainly true. The validity and reliability of the German self-administered version have been supported in past research [51, 52].

#### Perceived chronic stress

The self-administered Perceived Stress Scale (PSS) [53] assesses one’s own subjective stress in the last month. Participants will be asked to evaluate the ten items on how often they experienced certain states, e.g., “In the last month, how often have you been angered because of things that were out of your control?” or “In the last month, how often have you found that you could not cope with all the things you had to do?” on a 5-point Likert scale ranging from 0 (never) to 4 (very often), once at baseline and at close-out assessment immediately after the fourth clown visit. A global value of perceived stress is obtained from summing up all responses after reversing positive items. The German version of the PSS will be used [54], which has been proven valid and reliable within a German sample including adults and adolescents [54]. Only adolescents from the age of 11 years will complete this questionnaire, as it is not age-appropriate for younger children.

#### Evaluation of care staff

A self-administered questionnaire for care staff at the health care facilities assesses effects of clown visits on their own mood, the atmosphere within the care team, and the patients’ well-being after each of the four clown visits. The questionnaire was developed by the authors specifically for the study purpose on the basis of previously implemented research tools [32, 55]. The items were partly self-developed and partly translated into German, adopted according to the study’s objectives, newly designed and formulated in accordance with previous research [32, 55]. The questionnaire includes 20 items. Using a 4-point Likert scale from 1 (very negative) to 4 (very positive) with an additional fifth option (no change perceived), assigned care staff will assess the extent of individual changes according to specific emotion-related domains like energy level, concentration, sense of sympathy, or serenity. Following the same scaling, care staff is further asked to evaluate the impact of the clown visits on work related items like general atmosphere in the ward, teamwork within the care staff, or ability to provide empathic care to the patients.

### Potential control variables and moderators

#### Control variables (examiners)

The examiners that will carry out data collection procedures on-site will complete a self-administered questionnaire assessing the date of assessment, name of examiner, name of the health care facility, type of setting (group or individual), number of participants (if group setting), pseudonymized identification codes of participating children and adolescents, start and end time of the clown visit (duration), time of saliva sample collection (pre and post), and special incidents for each clown visit.

#### Sociodemographic and clinical data and control variables for salivary cortisol (children and adolescents)

A self-administered questionnaire to assess children’s and adolescents’ sociodemographic data includes information about gender, age, type of school attended before psychiatric admission, first language, and number of previously experienced clown visits. Further, psychiatric diagnoses or reasons for treatment, admission date at the clinic, number of previous clinic stays, current treatment (forms of therapy), current medication, attending in-house clinic schooling, and somatic comorbidities are assessed by a self-administered questionnaire filled out by care staff. Control variables for salivary cortisol are measured by a self-administered questionnaire completed by children and adolescents (i.e., intake of food, chewing gums, or relevant drinks (i.e., coffee, tea, cola, juices, and alcohol); tooth brushing or smoking within an hour before the collection of the saliva samples; whether they did sport in the last 48 hours; whether they took medication on the same day; and whether they feel healthy).

#### Sociodemographic data (care staff)

A self-administered questionnaire to assess care staff’s own sociodemographic data includes information about type of care staff, age, gender, extent and duration of employment in the relevant clinic, and first language.

#### Perceived enjoyment

A self-developed and age-appropriate self-administered 5-point Likert scale with one item assesses how participants and care staff enjoyed the clown visit from 0 (not at all) to 4 (very much) after each of the four clown visits.

#### Coping with stress

The self-administered Stress and Coping Questionnaire for Children and Adolescents (SSKJ 3–8) [56] is a German measure to assess stress and coping styles in children and adolescents. At baseline, participating children and adolescents will complete the coping style scale of the SSKJ 3–8, encompassing 30 items that describe coping strategies to reduce stress. Participants are prompted in written form to evaluate how regularly they exhibit the described behaviors on a 5-point Likert scale ranging from 1 (never) to 5 (always). These correspond to five subscales consisting of six items each, namely *seeking social support* (e.g., “I tell one of my family members what happened”), *problem-focused coping* (e.g., “I decide for a way to solve the problem”), *avoidance* (e.g., “I act as if everything was o.k.”), *constructive-palliative coping* (e.g., “I try to do something relaxing”), and *destructive-anger-focused coping* (e.g., “I get angry and destroy something”). The SSKJ has shown good validity (convergent, discriminant) and reliability (Cronbach’s alpha, retest) for all subscales [57].

### Statistical analysis

Due to the nested data structure (outcomes being nested within time points and in turn nested within participants), change in primary outcome measures (i.e., perceived stress and mood, salivary cortisol) will be analyzed by means of multilevel modeling using R packages (e.g., lme4 package [58]) to disentangle within-subject and between-subject variance. Level 1 comprises variables that are assessed repeatedly (i.e., the primary outcomes assessed before as well as immediately after each of the four clown visits), whereas level 2 specifies time points. Level 3 comprises of individual participants. Note that to prevent convergence issues, the best-fit model out of the following models will be used to test hypotheses: Fixed slope, random intercept for level 2 and 3 (Model 1); random slope at level 3 (Model 2); random slope at level 2 (Model 3); random slope at levels 2 and 3 (Model 4).

Given the complexity of the models, further analyses are to be considered exploratory in view of the small sample size of this pilot study. Potential moderator effects (number of visits, enjoyment, baseline variables) will be examined by testing cross-level interactions, provided the best-fit model allows for these analyses.

Missing data will be handled with full-information maximum likelihood (FIML) estimation, which uses all available information in the variance/covariance matrix to compute model parameters and produces less biased estimates than listwise or pairwise deletion or mean substitution [59]. Statistical significance will be assumed at α ≤ .05, as conventional. To reduce the chance of false discovery, alpha error correction will be applied using the Benjamini-Hochberg procedure [60].

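### Models 3 and 4 put a pre/post slope on visits that hold only two observations and are not identified in their usual form; choosing the tested model by fit can also ignore differences between participants in response

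*Protocol article*

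**What the plan says.** The Statistical analysis section of the protocol article describes three levels, with "outcomes being nested within time points and in turn nested within participants". Level 1 holds "the primary outcomes assessed before as well as immediately after each of the four clown visits", "whereas level 2 specifies time points", and "Level 3 comprises of individual participants".

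Four candidates follow: "Fixed slope, random intercept for level 2 and 3 (Model 1"), "random slope at level 3 (Model 2"), and then "random slope at level 2 (Model 3); random slope at levels 2 and 3 (Model 4"). The choice among them is made by fit: "the best-fit model out of the following models will be used to test hypotheses". The reason given is to avoid convergence problems.

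The section does not state a fit criterion, whether intercepts and slopes are correlated, how pre/post is coded, or what happens if a model fails. Significance is set at 0.05. The Participants section gives a minimum of about 30 participants and a target of at least 50.

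**The concern.** A random slope at level 2 needs a predictor that varies within a visit, and pre/post is the only one described. Each participant-visit supplies one value before and one after. A visit-specific intercept and a visit-specific slope are two random effects for two observations, which leaves nothing from which to estimate the residual. Half of the candidate list is then not usable in its usual form, and ranking by fit does not serve the aim of avoiding convergence problems.

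The second issue is which model remains for testing hypotheses 1 and 2 (lower stress, better mood and lower cortisol after a visit). Nothing requires the tested model to let the pre/post change differ between participants. Model 1 does not, so it counts a participant's four changes as four independent pieces of evidence. If some participants respond consistently more than others, its standard error is too small and the test rejects too often.

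**Working it through.** **Inputs.** Two observations per visit, four visits per participant and the four candidate models come from the Statistical analysis section. The numbers of participants (50 and about 30) come from the Participants section. The plan gives no figure for the candidate models themselves. Its sample size can be reproduced: a one-tailed paired t-test at 0.05 with 80% power and a standardised difference of 2f needs 31 participants for f = .23 and 27 for f = .25, which fits a minimum of about 30.

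**Step 1: identification within a visit.** Let the visit-level intercept variance be a, the slope variance b, their covariance c and the residual variance s. With pre = 0 and post = 1:

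- Var(pre) = a + s
- Var(post) = a + 2c + b + s
- Cov(pre, post) = a + c

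These are three equations in four unknowns. For any k, replacing (a, b, c, s) by (a + k, b + 2k, c − k, s − k) leaves all three unchanged. More participants do not help.

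Adding the three moments between different visits of the same participant gives, for each whole model, the number of variance parameters against the rank of the moment equations:

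- Model 1: 3 parameters, rank 3
- Model 2: 5 parameters, rank 5
- Model 3: 5 parameters, rank 4
- Model 4: 7 parameters, rank 6

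Models 3 and 4 are each one short.

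**Step 2: uncorrelated slopes.** With c = 0 and 0/1 coding, Models 3 and 4 are just identified (4 parameters with rank 4, and 5 with rank 5). But then b = Var(post) − Var(pre), which forces the post-visit variance to be at least the pre-visit variance. With c = 0 and −0.5/+0.5 coding they are again one short (4 with rank 3, and 5 with rank 4).

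**Step 3: software.** Fifty participants give 50 × 4 = 200 visits, 200 × 2 = 400 observations and 200 × 2 = 400 visit-level random effects. On simulated data of this shape, lme4 fitted Models 1 and 2. It stopped on the correlated Models 3 and 4 because observations did not exceed random effects (400 against 400). With 10% of observations removed, the same error came at 360 against 400.

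**Step 4: standard error without a participant slope.** Let ρ be the share of the variance V of a visit's change that lies between participants. The mean change has true variance V(1 + 3ρ)/(4n), while Model 1 uses V/(4n). The standard-error ratio is 1/√(1 + 3ρ), and the two-sided type I error is 2[1 − Φ(1.96/√(1 + 3ρ))]:

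- ρ = 0.1: ratio 0.88, error 8.6%
- ρ = 0.2: ratio 0.79, error 12.1%
- ρ = 0.3: ratio 0.73, error 15.5%

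The protocol gives no ρ, so these values are an assumed range.

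**Step 5: error after selection between Models 1 and 2.** Simulated with n = 50, complete data, two-sided 0.05 and 1,500 data sets per row (simulation error about 0.6 points near 5%). Entries are type I error in %:

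| ρ | Model 1 always | AIC | Likelihood-ratio test | BIC | Model 2 always |
|---|---|---|---|---|---|
| 0 | 5.6 | 5.3 | 5.5 | 5.6 | 4.6 |
| 0.1 | 9.3 | 6.3 | 7.3 | 8.3 | 4.8 |
| 0.2 | 11.7 | 5.7 | 6.7 | 8.7 | 4.8 |
| 0.3 | 15.5 | 5.5 | 5.7 | 7.0 | 5.3 |

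Model 1 was chosen in 59% (AIC), 75% (likelihood-ratio test) and 94% (BIC) of data sets at ρ = 0.1, and in 13%, 24% and 60% at ρ = 0.2.

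Two larger simulations with simplified tests (20,000 and 40,000 data sets per setting) gave the following at ρ = 0.1 and 0.2:

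- AIC: 7.0% and 6.2%; 6.8% and 6.1%
- BIC: 8.9% and 9.4%; 8.3% and 9.5%
- Likelihood-ratio test (first simulation only): 7.8% and 6.7%
- Participant slope always kept: 5.0–5.7%

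At n = 30 (1,200 data sets), ρ = 0.1 and 0.2 gave 6.8% and 7.8% with AIC, 7.4% and 8.8% with the likelihood-ratio test, 7.8% and 11.5% with BIC, and 4.2% and 5.8% for Model 2.

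**The case against.** A reader might infer that Models 3 and 4 cannot be estimated at all. The document does not support that. It states neither the correlation structure nor the coding, it names lme4 only as an example, and one form (Step 2) is just identified. Even in the unidentified form, the fixed pre/post effect can be computed if the software's check is overridden; what cannot be recovered is the split between visit-level variances and residual. A model that stops with an error also biases nothing: the analyst sees the error and is left with Models 1 and 2. All of this stands. It makes the first part a defect of the candidate list rather than a source of bias.

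A reader might also take 8.6–12.1% as the plan's error rate, or conclude that the rule generally picks Model 1. Neither follows. Those rates belong to always using Model 1, whereas the plan selects. How often it selects Model 1 depends on the criterion and on ρ: with AIC, 59% at ρ = 0.1 but 13% at ρ = 0.2. The criterion is a detail that an article may leave to a fuller document. Under AIC the excess is small, and only BIC gives a clear one.

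Finally, this is a single-arm pilot that itself says causal inference is precluded, so a few points of type I error weigh less than in a controlled trial. That bears on severity. It does not remove the point: the section labels only the further analyses exploratory, and naming a criterion elsewhere would still leave two problematic models on the list.

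**Conclusion.** The point holds in a limited form. Models 3 and 4 with a correlated intercept and slope are not identified from two observations per visit, and this rests on no assumed value. The one identified variant found is unspecified, depends on the coding and restricts the variances.

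The best-fit rule also allows hypotheses 1 and 2 to be tested with Model 1. Model 3 would not cure this, because a visit-level slope still treats a participant's four changes as independent. With ρ of 0.1–0.2 assumed, 50 participants and complete data, type I error after selection is about 6–7% (AIC), 7–8% (likelihood-ratio test) or 8–10% (BIC), against 5–6% with the participant slope always kept. With ρ = 0 there is no inflation.

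Severity is should-fix. A reading that the pilot's main tests are invalid would go beyond what the document and these figures support.

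**What to change.** Delete Models 3 and 4. Prespecify Model 2 (random intercepts at levels 2 and 3, random pre/post slope at level 3) for all primary tests, with no selection by fit.

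State the fallback in order:

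1. If Model 2 does not converge, drop the intercept-slope correlation and keep the slope.
2. If it still fails, or the slope variance is estimated at zero, use a t-test on each participant's mean pre/post change.

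The second step is needed because a zero slope variance reduces the fit to Model 1. In simulation this happened in 55%, 25% and 8% of data sets at ρ = 0, 0.05 and 0.1.

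Report Model 1 as a sensitivity analysis only. The cost is a few lines of wording and slightly wider intervals when slopes hardly vary. The sample size does not change.

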There are several strengths of this study. We will assess children’s and adolescents’ stress levels by subjective (self-report) as well as physiological measures (salivary cortisol), which enables us to measure the immediate effect on stress on two different levels, enhancing the validity of assessments. The inclusion of secondary outcomes provides further insights of the overall impact of the four-week intervention. As staff reports are collected as well, conclusions can be drawn from various perspectives. Experiences of care staff have only been included in a limited number of studies so far. More attention to this area is needed, as those few studies found positive effects of healthcare clowning on care staff and their working conditions in psychiatric settings [28, 31, 32]. Additionally, control and moderator variables are assessed. Thereby, we will be able to account for statistical controls as well as to identify potential subgroups benefiting most from interventions. Moreover, the repeated measures design (i.e., one clown visit on a weekly basis over four consecutive weeks) allows the investigation of cumulative effects as a result of repeated clown visits.

Although this pilot study aims at closing an important research gap, we are also aware of its limitations. First, the lack of an untreated control group will preclude causal inferences. Thus, there is a chance that alternative explanations such as other temporal developments could account for found effects rather than the intervention per se. However, as assessments take place before and after each clown visit, within-subject temporal trends can still be examined. Second, due to the target sample size of approximately 50 children and adolescents and the circumstance that the study only takes place in two facilities, generalizability of study results is inherently limited. Third, not all questionnaires used in this study have been validated in previous research. We must therefore first examine whether the instruments in question, which were developed on the basis of theoretical considerations, also prove themselves empirically.

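### Enjoyment, rated only after each visit, is listed as a moderator of that visit's pre/post change; a same-visit interaction can appear when every child changes equally

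*Protocol article*

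**What the plan says.** All references are to the protocol article.

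- **Statistical analysis** puts enjoyment in one list with number of visits and baseline variables: "Potential moderator effects (number of visits, enjoyment, baseline variables) will be examined by testing cross-level interactions". These tests are conditional on the best-fit model allowing them. The preceding sentence says that "further analyses are to be considered exploratory in view of the small sample size of this pilot study". The section also sets α at .05 and applies the Benjamini-Hochberg procedure.
- **Perceived enjoyment** describes a single item on "how participants and care staff enjoyed the clown visit from 0 (not at all) to 4 (very much) after each of the four clown visits". No baseline or pre-visit rating is described.
- **Perceived stress** is self-rated "using a 100-mm visual analogue scale (VAS) before as well as immediately after each of the four clown visits".
- **Perceived mood** is a self-report of "current mood states (pleasant–unpleasant; awake–sleepy; calm–restless) before as well as immediately after each of the four clown visits".
- **Salivary cortisol** is an assay: "Samples will be collected immediately before as well as immediately after each of the four clown visits".
- **Discussion** counts the control and moderator variables among the study's strengths, because they allow the authors "to identify potential subgroups benefiting most from interventions".

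**The concern.** A moderator that is meant to show who benefits should be settled before the change it is supposed to modify. Baseline variables meet that condition. Enjoyment of a visit does not: it is a reaction to the visit, given by the same child in the same post-visit window as the second half of the stress or mood difference.

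Anything that lifts a child's state at that moment, including rating noise, raises the post-visit score and may raise the enjoyment rating too. The pre-visit score does not share it. Enjoyment then correlates with the difference even if the visit does exactly the same for every child.

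At stake is the reading of this one exploratory result. A significant interaction could be reported as showing that children who enjoy the clowns benefit most, when it shows only that two ratings made in the same window agree.

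**Working it through.** **Plan's own figure.** The article gives none for this analysis. Its sample size is reproducible: a one-tailed paired t-test with α = .05, power .80 and the smallest effect, f = .23, read as dz = 2f = .46, gives N = 31 against the stated figure of about 30. Nothing below depends on it.

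**Inputs from the article.** N = 50 (target), four visits, so 50 × 4 = 200 visit-level changes; α = .05; enjoyment on five points (0 to 4), once per visit.

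**Assumptions not in the article.** Two-sided test before any multiplicity correction; pre-post correlation ρ from .5 to .8; size r of the correlation between enjoyment and the post-visit state from 0 to .5, with a better state going with higher enjoyment; the moderator is the child's own same-visit rating; every child has the same true change of half a standard deviation, so there is no moderation.

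**Closed form.** Give pre and post unit variance.

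- Enjoyment has covariance r with post and rρ with pre, so its covariance with the change is r − rρ = r(1 − ρ).
- The change has variance 2(1 − ρ).
- The correlation of enjoyment with change is therefore r(1 − ρ)/√[2(1 − ρ)] = r√[(1 − ρ)/2]. It is not zero, although the true change is constant.
- Over 200 changes the expected test statistic is about δ = r√[(1 − ρ)/2] × √200, and the rejection rate is Φ(δ − 1.96) + Φ(−δ − 1.96).

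Example: for r = .3 and ρ = .5 the correlation is .3 × .5 = .15, δ = .15 × 14.14 = 2.12, and the rate is 56%.

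| r | δ at ρ = .8 | rate | δ at ρ = .5 | rate | simulated, ρ = .8 to .5 |
|---|---|---|---|---|---|
| .1 | 0.45 | 7% | 0.71 | 11% | 7-11% |
| .2 | 0.89 | 15% | 1.41 | 29% | 11-26% |
| .3 | 1.34 | 27% | 2.12 | 56% | 24-54% |
| .5 | 2.24 | 61% | 3.54 | 94% | 55-93% |

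The last column is from simulations that regress each visit's change on a five-category enjoyment score. The coarser score explains most of the small gap: it correlates about .95 with the underlying continuous score, and multiplying δ by .95 gives 7-10%, 14-27%, 25-52% and 56-92%. At r = 0 the simulated rate is 5-6%.

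**Other settings.**

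- *Mixed model with random intercepts for visit and child, as in Model 1* (ρ = .6; 100 runs each, so a standard error of about 5 points near 50%): 5% at r = 0, 53% at r = .3, 92% at r = .5.
- *30 children instead of 50:* 7-8%, 11-17%, 17-36% and 37-75% for r = .1, .2, .3 and .5.
- *Enjoyment as the child's mean over visits:* about 8-36% over r = .2 to .5; at ρ = .6 specifically 8%, 14% and 25% for r = .2, .3 and .5.
- *Enjoyment related only to the part of the state shared by pre and post* (r = .5): 5%.
- *Previous visit's enjoyment against the next visit's change, no carry-over of state:* 4-6%.
- *The same with carry-over of .4 from one visit to the next:* over r = .2 to .5, 8-19% at ρ = .5 and 7-12% at ρ = .8. A separate run at ρ = .5 with carry-over of .3 to .5 reached 14-33% at r = .5.

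**The case against.** The other side has several fair points.

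- **The analysis is exploratory and conditional.** This is true, and no stated hypothesis concerns enjoyment, so the stakes are limited. But the exploratory label warns of imprecision and chance findings; it does not remove a bias. Benjamini-Hochberg does not either, because the excess rejections do not come from multiple testing.
- **The coding of enjoyment is not spelled out.** A rating made once per visit belongs naturally at the time-point level, but the article does not exclude a person mean, and such detail may sit in an analysis plan not shown here. A person mean lessens the problem without removing it. The article itself makes the choice to call enjoyment a moderator.
- **Simultaneity is inferred.** Enjoyment is rated after the visit, the outcomes immediately after. The order of items cannot be checked. Both still fall in the post-visit window.
- **The size is assumption-dependent.** This stands. With r near .1 the excess is small.
- **Cortisol is an assay.** This stands. There is no shared rater, so cortisol is affected only as far as enjoyment tracks post-visit cortisol.
- **Lagging is not a clean cure.** This stands too: with carry-over between visits, earlier enjoyment predicts the next pre-visit score, and some bias remains.

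A reader might also infer that the article intends the enjoyment interaction to steer a later randomised trial. It does not say so. The remark on subgroups covers control and moderator variables together, and the relevance to future trials is claimed for the results as a whole.

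**Conclusion.** The point holds in limited form. Treating same-visit enjoyment as a moderator beside baseline variables can yield a significant interaction when every child changes equally. With 50 children and four visits, the false-positive rate runs from near nominal (7-11% at r = .1) to severe (55-93% at r = .5). The values of r and of the pre-post correlation are assumptions; the article gives neither.

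A reader might infer that the plan is bound to produce a false moderation finding. The documents do not support that: the rate stays at 5% if enjoyment tracks only what pre and post share, and it is lower with a person mean. Nor does the point reach the pre/post hypothesis tests or the sample size. It concerns one exploratory analysis, chiefly for self-reported stress and mood.

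**What to change.** In Statistical analysis, remove same-visit enjoyment from the list of moderators. State that it will be reported as a correlate, or process measure, of the post-visit score or change, and not as evidence of which subgroups benefit most. Make the Discussion sentence on subgroups consistent with this.

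If a moderator test is still wanted, use enjoyment from earlier visits (the previous visit, or the mean of all earlier ones) for the change at the next visit, and state three limits:

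- visit 1 drops out of this test;
- the question becomes whether earlier enjoyment predicts later change;
- some bias may remain if state carries over from one visit to the next.

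The cost is one or two sentences. No new data are needed, and no other analysis changes.
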